### Data management and statistical analysis

We will design our study forms in REDCap (Research Electronic Data Capture), a secure web data capture tool developed by Vanderbilt University that offers a range of functions to collect, store, and analyze basic data from the desired population. Forms will be stored and de-identified in REDCap with access to all study researchers and the REDCap data manager of the Faculty of Medicine of Eduardo Mondlane University. The forms will be exported to SPSS (Statistical Package for Social Sciences) version 25 for statistical analysis.

Quantitative data analysis

Descriptive and inferential statistical analysis deemed relevant based on collected data will be performed. The descriptive analysis will be based on the elaboration of absolute and relative frequency tables and charts. To explore the factors associated with antibiotic prescribing and the need for antibiotic prescribing, multivariate logistic regression analysis will be performed. The dependent variables to be considered separately will be the prescription of antibiotics and the need for the antibiotic. Each dependent variable will be crossed with the possible factors (independent variables). ANOVA will be used to test differences among sites within the same group for both intervention and control sites with a significance level of 5%.

To compare the effect of the intervention between the intervention and control sites, Pearson's chi-square test will be used, with a significance level of 5%. To verify the magnitude of the effect of the intervention, the relative risk (RR) will be calculated and to estimate the effectiveness of the intervention, the effectiveness ratio (1 – RR) will be determined. For inferential analysis, the 95% confidence interval will be calculated for the RR parameter.

For power calculation, we have set alpha equal to 0.05 and 80% power to detect differences in proportion greater than or equal to 0.15. In other words, if we get a reduction of 15% of the overall antibiotic rate in the intervention sites compared to control sites, we could detect a significant change in proportion. We assumed a coefficient of variation equal to 0.2 for this estimate.

Quantitatively, satisfaction will be measured as the degree of satisfaction of the prescribing clinicians at the intervention study sites using the CDSA. To identify the factors that influence their degree of satisfaction using the CDSA, a multivariate logistic regression analysis will be performed. For the dependent variable, the satisfaction of clinicians, the 5-point Likert scale will be reduced to a binary category of dissatisfied (very dissatisfied, dissatisfied, neutral) and satisfied (very satisfied, satisfied). Potential factors that influence satisfaction to be considered are sex, age, length of time in current position, and the professional category of the health worker.

Qualitative data analysis

Qualitative data will be coded and analyzed using qualitative analytic software (*NVivo version 12*). Audio recordings will be transcribed and coded using constructs consistent with our study aims and relevant implementation outcomes (adoption, acceptability) which will be outlined in a codebook with definitions. After encoding the constructs, a directed content analysis approach with allowance for the emergence of new themes will be used. After the qualitative analysis, we will perform a quantitative analysis of the contents or themes using a frequency table to be created in the Excel program.

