**Methods:**

This study is a multicenter, two-arm, cluster randomized controlled trial, involving six primary health care facilities in Maputo and Matola municipalities in Mozambique, guided by an innovative implementation science framework, the Dynamic Adaption Process. In total, 380 HIV-infected patients with URTI symptoms will be enrolled, with 190 patients assigned to both the intervention and control arms. For intervention sites, the CDSAs will be posted on either the exam room wall or on the clinician´s exam room desk for ease of reference during clinical visits. Our sample size is powered to detect a reduction in antibiotic use by 15%. We will evaluate the effectiveness and implementation outcomes and examine the effect of multi-level (sites and patients) factors in promoting the de-implementation of unnecessary antibiotic prescriptions. The effectiveness and implementation of our antibiotic de-implementation strategy are the primary outcomes, whereas the clinical endpoints are the secondary outcomes.

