### Randomization within the two-arm cluster randomized trial and characteristics of the study participants

To mitigate contamination threat to internal validity among participating facilities, randomization and allocation will be primarily among the 10 administrative units (primary clusters). Primary clusters are considered municipal districts (Maputo) or administrative posts (Matola). Randomization will be performed before the initiation of our pre-implementation phase. Initially, randomization will be undertaken through the generation of a sequence of random numbers corresponding to each primary cluster. A total of six primary clusters will be randomly assigned to either the intervention or control arms (three each). Afterwards, in each selected primary cluster only one primary healthcare facility (secondary cluster) will be randomly selected to participate in the study. All participants in the same facility will be assigned to the same treatment, either intervention or control. A statistician will generate the allocation sequence and assign participating healthcare facilities to intervention or control groups.

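### Effects of site and patient factors are promised, but the only factor model named makes no stated allowance for facility, and there are six facilities

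*Protocol article*

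**What the plan says.** The abstract (Methods) states that the trial will "examine the effect of multi-level (sites and patients) factors in promoting the de-implementation of unnecessary antibiotic prescriptions".

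The randomization section allocates six primary clusters, three to each arm, and "in each selected primary cluster only one primary healthcare facility (secondary cluster) will be randomly selected". There are therefore six facilities.

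Under Quantitative data analysis, the model for associated factors is given as: "To explore the factors associated with antibiotic prescribing and the need for antibiotic prescribing, multivariate logistic regression analysis will be performed". Prescription of an antibiotic and need for one are the two outcomes, each modelled separately. The candidate factors are not listed, and no random effect, cluster-robust variance, facility term or site-level summary is mentioned.

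Site appears once more in that section: "ANOVA will be used to test differences among sites within the same group". The arms are compared by an ordinary Pearson chi-square test. The power paragraph adds: "We assumed a coefficient of variation equal to 0.2 for this estimate". It does not say what this coefficient describes.

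**The concern.** A site characteristic, such as laboratory capacity or medicine availability (both assessed in phase one), has one value per facility and so at most six values in the trial. Logistic regression on individual patients treats 380 responses as independent. If facilities differ in prescribing for reasons outside the model, the standard error of a site factor is too small and its p-value is misleading. The plan itself appears to expect such differences, since it assumes a coefficient of variation and schedules a test among sites.

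The ANOVA does not repair this. It asks whether sites within an arm differ, but it does not change the standard errors in the regression.

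For patient-level factors the risk is of another kind. If patient mix and prescribing habit both vary by facility, omitting facility can mix the two in the odds ratio.

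Correcting the arm comparison for clustering would leave this regression unchanged, so it needs its own sentence in the plan. At stake is the reliability of any statement about which site features go with unnecessary prescribing.

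**Working it through.** The plan gives no figure for this regression, so there is none to reproduce. Its sample-size statement concerns the arm comparison.

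**Inputs**

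- 380 patients (abstract) in six facilities (randomization section). With equal sizes, assumed here, m = 380/6 = 63.3 per facility.
- Coefficient of variation k = 0.2 (power paragraph), read as the between-facility standard deviation divided by the mean rate. This reading is an assumption. Other values of k are shown for range.
- Antibiotic rate p = 65.9% (Background), from earlier outpatient work in HIV-infected patients. It is the only local figure and is not stated to be an input to the power calculation. A rate of 50% is the alternative.

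**Formulas**

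- Intracluster correlation: ICC = (k·p)² / [p(1 − p)] = k²·p/(1 − p)
- Design effect: DE = 1 + (m − 1)·ICC
- True error of a nominal two-sided 5% test of a purely site-level factor: 2·[1 − Φ(1.96/√DE)]

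**At k = 0.2 and p = 0.659**

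- ICC = 0.04 × 0.659/0.341 = 0.0773
- DE = 1 + 62.3 × 0.0773 = 5.82
- Effective sample size for a site factor = 380/5.82 = about 65
- 1.96/√5.82 = 0.81, giving a two-sided error of about 42%

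**Range.** The simulation used six sites of 63 or 64 patients, beta-distributed site rates and 3,000 runs. Its logistic model held arm, a binary site factor and a patient factor, all without effect.

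| Rate | k | ICC | DE | Error, formula | Error, simulation |
|---|---|---|---|---|---|
| 65.9% | 0.05 | 0.0048 | 1.30 | 8.6% | 10.1% |
| 65.9% | 0.1 | 0.0193 | 2.20 | 18.7% | 19.4% |
| 65.9% | 0.2 | 0.0773 | 5.82 | 41.6% | 42.9% |
| 50% | 0.05 | 0.0025 | 1.16 | 6.8% | 6.9% |
| 50% | 0.1 | 0.0100 | 1.62 | 12.4% | 14.1% |
| 50% | 0.2 | 0.0400 | 3.49 | 29.4% | 30.2% |

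At 65.9% the simulated error was 5.5% with no facility variation and 58% at k = 0.3. A separate simulation (20,000 runs, 3-versus-3 site factor, no other covariates) gave 43%, 18% and 9% at a 65.9% rate for k = 0.2, 0.1 and 0.05, and 29%, 11% and 6% at a 50% rate.

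**Two contrasts from the first simulation**

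- A patient factor unrelated to facility was rejected in 4.0% to 5.6% of runs across all settings, so its test is not materially inflated.
- The same site factor, tested by regression on the six facility proportions, was rejected in 4.3% to 6.4% of runs. That test has 6 − 3 = 3 residual degrees of freedom, after intercept, arm and the factor.

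**The case against.** The strongest reply is that the defect is partly inferred. The analysis section lists no factors, so facility could be among them, and an article may leave model detail to a fuller document. No text says that site characteristics enter this regression. The site features named above come from phase one, whose data are described as qualitative. The abstract's promise could be met by the ANOVA or by the descriptive implementation evaluation. The analysis is also exploratory, and no significance level is attached to it.

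Much of this stands and limits the claim. It does not remove it. The article does name a method, and that method, read beside a plain chi-square test, does not fit the multi-level aim in the abstract. No other model in the article relates prescribing to factors.

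A reader might go further and infer any of the following, which the documents do not support:

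- *Site factors will be declared significant largely by chance.* The error depends on an unstated meaning of the coefficient and on the rate. At a coefficient of 0.05 it is only modestly above 5%, and no decision rule is given.
- *The patient-level odds ratios are confounded.* That requires patient mix to differ by facility, which nothing in the article shows.
- *P-values for site factors must be abandoned.* A test on the six facility rates stays close to its nominal level. It is imprecise, but valid.

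**Conclusion.** The point holds in conditional form. The one factor model named has no stated allowance for facility and does not suit the promised site-level part of the analysis. If site factors enter it as written, a nominal 5% test of a null factor has a true error of about 43% at a coefficient of 0.2 and a 65.9% rate, about 30% at a 50% rate, and about 6 to 10% at an assumed coefficient of 0.05. These figures rest on reading the coefficient as between-facility variation and on equal facility sizes. For patient-level factors the issue is possible confounding by facility, and its size cannot be given from the documents. Because the analysis is exploratory, the trial's main conclusion does not depend on it, but the plan should be corrected.

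**What to change.** Under Quantitative data analysis, split the factor analysis in two, for both outcomes:

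1. **Patient-level factors.** Fit the logistic regression with facility as a fixed effect (five indicators, which absorb arm). Report only the patient-level odds ratios from it.
2. **Site-level factors.** Examine these only on the six facility-level rates. Either tabulate the rates against each factor, or use a site-level test with small-sample degrees of freedom (about 3 for one factor after arm). Report the results as exploratory.

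State which factors belong to which level, and say that the abstract's site-level aim is met by the second part. A mixed model or generalized estimating equations would not by themselves solve the site-level problem, because six facilities still leave about 3 degrees of freedom.

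The cost is analysis wording and five extra parameters in a model on 380 patients. Enrolment and data collection are unaffected. The downside is that arm and site factors cannot be estimated in the fixed-effect model, and that inference on any site factor will be very imprecise.

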### Study design and conceptual frameworks

We propose a multicenter two-arm cluster randomized controlled trial that will employ a mixed-methods approach. This study will be guided by two conceptual frameworks, the Dynamic Adaptation Process (DAP) and the Reach, Effectiveness, Adoption, Implementation, and Maintenance (RE-AIM) framework, and will be carried out in three phases (Fig. 1). The DAP framework was developed to provide the structure for an iterative process to guide, monitor, and evaluate the introduction of a new intervention into practice. DAP is a framework that allows changes to be made according to the real context by the possibility of tailoring the elements of the intervention based on data obtained during the pre-implementation and the adaptation. DAP engages stakeholders at all levels to develop robust implementation strategies and will guide the work of phases one, two, and three in our study [29]. *Phase one* (pre-implementation) will consist of a formative baseline evaluation of the current situation for antibiotic prescribing for URTI in the outpatient setting among PLHIV and occur over three months. It will consist of interviews with identified health workers to understand the current antibiotic prescribing practices for URTI among HIV-infected ambulatory patients, as well as perceived facilitators and barriers to the roll-out of our de-implementation strategy. A document review will be performed to identify the existence of national guidelines or normative documents driving antibiotic prescribing for URTI. Phase one will also include documentation of current laboratory diagnostic capacity for URTI and a situational assessment of the availability of medicines to treat URTI. *Phase two* (adaptation and implementation) consists of our de-implementation strategy roll-out and will occur over six months. Based on information learned in phase one, we will make workflow adjustments to address realities on the ground. The CDSA will be rolled out within a two-arm cluster randomized control trial design in which our primary outcome measure will be the clinical decision to use antibiotics or not. Intervention elements and study tools will be adapted before the intervention is implemented. Throughout this phase, an implementation audit and continuous feedback will be conducted to guarantee and monitor adherence to the intervention protocol. *Phase three* (post-implementation) will consist of a three-month post-implementation phase in which we will analyze implementation outcomes and processes as a function of the RE-AIM conceptual framework, in real-time. *Reach* will be assessed in terms of patient recruitment, refusal, and attrition. *Effectiveness* will be analyzed by comparing antibiotic use rates and patient-related clinical outcomes between the intervention and control arms. For *adoption*, clinicians who adopted the practice of de-implementation of unnecessary antibiotic use will be assessed using prescriptions and clinical records. For *implementation*, the fidelity and satisfaction of clinicians regarding the intervention will be assessed. For *maintenance*, sites and clinicians that maintain de-implementation practices and use of the CDSA will be assessed one year after completion of the intervention.

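### The arms are compared with a Pearson chi-square test and an RR interval with no stated allowance for clustering, although six facilities are randomised 3 versus 3, so the nominal 5% level does not hold

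*Protocol article*

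**What the plan says.** All references are to the protocol article; no separate SAP is shown.

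- **Design.** The section on randomization allocates six administrative units, three per arm, and selects one facility in each. "All participants in the same facility will be assigned to the same treatment, either intervention or control". The facility is therefore the unit of randomisation.
- **Outcome.** Under study design: "our primary outcome measure will be the clinical decision to use antibiotics or not". It is a yes/no variable recorded per patient, with 190 patients planned per arm.
- **Arm comparison.** Under Data management and statistical analysis: "between the intervention and control sites, Pearson's chi-square test will be used, with a significance level of 5" per cent. The effect is expressed as RR and 1 − RR, and "For inferential analysis, the 95% confidence interval will be calculated for the RR parameter".
- **Power.** The same section states: "we have set alpha equal to 0.05 and 80% power to detect differences in proportion greater than or equal to 0.15". It adds: "We assumed a coefficient of variation equal to 0.2 for this estimate". It does not say which quantity the CV describes and gives no control-arm rate.
- **Other mentions of sites.** "ANOVA will be used to test differences among sites within the same group", and the abstract's plan to "examine the effect of multi-level (sites and patients) factors". Neither is tied to the comparison between arms.

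**The concern.** An ordinary Pearson chi-square test on a patient-level yes/no outcome takes its variance from 380 independent patients. Here the arms differ by which three facilities fell into each, and prescribing habits are likely to be shared within a facility. The chi-square variance leaves out that between-facility component. Chance differences between two sets of three facilities can then be reported as an intervention effect, with an RR interval that is too narrow.

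The article foresees extending the strategy to further facilities on the strength of these results. A false positive would therefore have practical consequences.

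**Working it through.** **Inputs.** From the article: 3 facilities per arm, 190 patients per arm (mean size m = 190/3 = 63.3), alpha 0.05, 80% power, difference 0.15, CV k = 0.2. Prescribing rates p come from the Background: 50–70% for URTI generally, and 65.9% in earlier local outpatient work. Neither is given as the control rate of this trial, so they are used as a range. Reading k as the between-facility CV of the prescribing proportion is an assumption.

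**1. The plan's own figure of 190 per arm.** Ignoring clustering, the two-sided two-proportion formula for a 0.15 absolute difference needs:

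- 170 per arm for 0.50 v 0.35
- 174 per arm for 0.575 v 0.425
- 169 per arm for 0.659 v 0.509

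With 190 per arm the power is about 84–85%. An assumed 10% dropout raises these numbers to 189, 194 and 188. So 190 fits an individually randomised calculation with an unstated allowance, but this cannot be confirmed.

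With k as between-facility variation, the facilities needed per arm are

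c = 1 + (1.96 + 0.84)² × v / 0.15², where v = [p0(1−p0) + p1(1−p1)]/m + k²(p0² + p1²).

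- Control 0.50: v = 0.0075 + 0.0149 = 0.0224, so c = 8.8, or about 9.
- Control 0.659: v = 0.0075 + 0.0277 = 0.0352, so c = 13.3, or 13–14.

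The design has 3.

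**2. Type I error of the unadjusted chi-square at k = 0.2.** The between-facility variance is (kp)², so ICC = k²p/(1−p). The design effect is DE = 1 + (m−1) × ICC, and the actual level is 2[1 − Φ(1.96/√DE)].

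| p | ICC | DE | Formula | Simulated | RR interval coverage |
|---|---|---|---|---|---|
| 0.50 | 0.040 | 1 + 62.3 × 0.040 = 3.49 | 29% | 29% | 71% |
| 0.659 | 0.04 × 0.659/0.341 = 0.077 | 5.82 | 42% | 42% | 58% |
| 0.70 | 0.04 × 0.70/0.30 = 0.093 | 6.82 | 45% | 46% | 54% |

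The simulations use beta-distributed facility rates, 63/63/64 patients per arm and no true effect.

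**3. Sensitivity.**

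- Smaller k, over p = 0.50–0.70: at CV 0.1 the type I error is about 12–22%; at CV 0.05 it is about 6–9%.
- Lower prescribing rate: p = 0.35 with k = 0.2 gives about 20%.
- If 0.2 describes something else, such as cluster size, no ICC is available. Assumed ICCs of 0.01, 0.02 and 0.05 (equal cluster sizes) give about 12%, 19% and 33%.

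**4. The valid alternative.** A t-test with 4 degrees of freedom on the six facility proportions, or their logs, has a simulated type I error of about 5% in all these p and k scenarios.

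Its power for a 0.15 drop at k = 0.2 follows from SE = √(v/3):

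- Control 0.50: SE = 0.0865, noncentrality 0.15/0.0865 = 1.73, power about 27%.
- Control 0.659: SE = 0.108, noncentrality 1.38, power about 19% by formula and 20–21% by simulation.

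**5. Permutation test.** There are C(6,3) = 20 possible allocations, so the smallest two-sided p-value is 2/20 = 0.10.

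**The case against.** **A later SAP could handle clustering.** It could, but the article is not silent. It names a test, a level and an interval for the arm comparison. A stated analysis that does not suit the design is different from a detail left for later.

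**The size is conditional.** This stands. A reader might infer that the plan's own CV fixes a particular false-positive rate. It does not: the CV is unlabelled and no control rate is given. The percentages hold only under the stated reading and range, and at CV 0.05 the inflation is modest. The direction does not depend on these choices.

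**The RR interval method is not written out.** True. A patient-level interval is the natural reading next to a chi-square test, and the coverage figures rest on it.

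**Sites are considered elsewhere.** The ANOVA compares sites within an arm and does not enter the arm comparison. The abstract's multi-level wording concerns factors. A reader might go further and infer that the logistic models of factors also ignore facility. The article does not support that: their covariates are left open, and site could be one of them.

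**A facility-level test leaves little power.** This also stands and must be disclosed. It is no reason to keep a test whose level is wrong.

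**Covariate adjustment could recover precision.** Only with care. Clinicians identify patients after allocation, and only intervention clinicians are trained on an algorithm that turns on symptom duration and signs of bacterial infection. Recording of those items may differ by arm, so adjusting for them could introduce bias.

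**Conclusion.** The point holds for the arm comparison as written: the test and, on its natural reading, the RR interval do not respect the unit of randomisation. The primary p-value and interval would not have their stated properties, and this must be corrected before the data are analysed.

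The 29–46% error rate and 54–71% coverage rest on two assumptions: that CV 0.2 is between-facility variation in prescribing, and that the rate is 50–70%. The finding does not extend to the factor models or the within-arm ANOVA. The stated 80% power does not carry over to a valid analysis of six facilities at CV 0.2.

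**What to change.** 1. Replace the chi-square test with an unadjusted facility-level primary analysis: compute each facility's antibiotic proportion and compare arms by a t-test with 4 degrees of freedom on the six (log) proportions.
2. Derive RR, 1 − RR and the 95% interval from the same analysis. On the log scale, exponentiate the difference in means and its limits, using the t distribution with 4 degrees of freedom. Report all six facility proportions.
3. Use the same approach for arm comparisons of the secondary outcomes.
4. Keep as sensitivity analyses only a mixed model with a small-sample degrees-of-freedom correction, or covariate-adjusted facility summaries. Limit adjustment to covariates whose recording cannot differ by arm, such as age and sex. Do not rely on a permutation test, which cannot reach 5% here.
5. State what the CV of 0.2 describes and which control rate was assumed, and restate the power.

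**Cost.** No new patient data are needed; facility identity is inherent in the design. Recruitment has begun, so the change should be documented before outcomes are examined by arm. The real price is wider intervals and power of about 20–27% for a 0.15 drop at CV 0.2. Rewording the analysis does not remedy that; only more facilities would restore power materially.
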